We also identified particularly vulnerable populations that may not be included in the study: (a) patients suffering from epilepsy because HMD can provoke epileptic seizures like other devices that produce visual effects (as described in the HTC-VIVE official user's guide); (b) visually impaired patients and hearing impaired patients because they would have limitations in the use of the virtual experience concerning sounds and visual aspects; (c) patients with cardiovascular problems because our psychophysiological measures of interest could be altered by these pathologies; (d) gamblers with vestibular problems because they may fall during the virtual reality experience due to vertigo, motion sickness, and imbalance (73); (e) patients with neurological disorders: e.g., individuals with migraine are more susceptible to visual discomfort (74); (f) patients with schizophrenia or psychotic traits because the available data on immersive VR in schizophrenic subjects are currently limited (75), and no data were available on gamblers with psychotic diseases and immersive VR treatment.

Patients with the onset of cybersickness for two consecutive virtual sessions will exit from the study *in itinere* and will be able to undertake a path of psychotherapy as usual in the Addiction Medicine Unit.

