Patients meeting the inclusion criteria will be randomly assigned to the CBT group or to the CBT + VR group. The CBT group will follow a full cycle of psychotherapy that will consist of 16 weekly sessions, lasting 60 min and will make use of techniques belonging to an evidence-based cognitive-behavioral approach. For the CBT + VR group, there will be a first cycle of traditional psychotherapy that will consist of 8 weekly sessions, each lasting 60 min, which will also make use of evidence-based cognitive-behavioral approach techniques. Following this, psychotherapy based on virtual exposure will be carried out, which will again comprise 8 weekly sessions, marked by: systematic desensitization therapy in virtual reality exposure therapy, cognitive restructuring, and emotional management/literacy. Each virtual session will last 60 min, 20 min of which will be dedicated to virtual exposure. About 20 mins is the recommended limit of the duration of immersions in virtual reality because eyestrain and headache may occur for longer exposures (76, 77). We adopted this safety limit at least until empirical data document the safety of VR immersion with gamblers (10). An extinction process needs more time to originate, but limiting the duration of the immersion is necessary due to ethical considerations (10).

The virtual session will be structured as follows. In the first session, the virtual protocol will be presented to the patient, and virtual training will be carried out to provide the skills related to the use of the instrumentation (Figure 11). Biofeedback parameters will also be measured 5 min before the session. From the second to the eighth sessions, the biofeedback parameters will be measured 5 min before the beginning of the session (in the study, the baseline rate), and the measurements will be resumed during the entire exposure to the virtual environment. The patient will be asked about the intensity of the craving felt during both measurements and at the end of each session *via* VAS. As mentioned above, the technique used in conjunction with virtual cue exposure therapy will be systematic desensitization, which is a psychotherapeutic CBT treatment consisting in alternating phases of exposure to the trigger cues to phases of bodily relaxation, with the aim of reinforcing the relaxation response even in the presence of specific reactive cues (78, 79).

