	**Week 0**	**Week 1**	**Week 2**	**8 weeks**	**8 weeks**	**Week 19**	**Week 20**	**Week 25**
Design and implementation of virtual environments								
Hardware and software installation and testing								
Training course for Treatment Providers								
First phone contact with patient								
Patient informed consent obtaining								
Data collection about the patient demographic characteristics, medical history and clinical history concerning GD								
Pre-test (MCMI-III, BIS-11, SOGS, GRCS, MGSES)								
Restitution of pre-test results to the patient								
Inclusion/exclusion criteria + randomization into CBT group and CBT + VR group								
First psychotherapy cycle (8 sessions of traditional psychotherapy for both groups)								
Second psychotherapy cycle (8 sessions of traditional psychotherapy for CBT group and 8 sessions of psychotherapy based on virtual reality for CBT + VR group)								
Post-test (MCMI-III, BIS-11, SOGS, GRCS, MGSES)								
Restitution of post-test results to the patient								
1-month follow-up (MCMI-III, BIS-11, SOGS, GRCS, MGSES)								

*GD, gambling disorder; MCMI-III, Millon Clinical Multiaxial Inventory-III; BIS-11, Barratt Impulsiveness Inventory-11; SOGS, South Oaks Gambling Screen; GRCR, Gambling Related Cognitions Scale; MGSES, Multidimensional Gambling Self-Efficacy Scale; CBT, cognitive behavioral therapy; VR, virtual reality*.

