## Data Analysis

In general, all the patients' demographic and clinical characteristics will be summarized using descriptive statistical methods. In particular, mean, median, and standard deviations will be used for symmetrically distributed continuous variables, median and interquartile distance for asymmetrically distributed continuous variables, and frequency distributions for categorical variables. Multi-method analysis of craving measurement in order to draw up a physiological and psychometric profile of craving (using biofeedback) will be performed. This analysis will be conducted through linear correlation measures. For the analysis of the efficacy of the training course for the treatment providers, Student's *t*-tests for dependent samples or Wilcoxon's non-parametric test for paired samples will be used. Contingency tables and McNemar tests may also be used. For the analysis of the efficacy of the CBT + VR group compared to the CBT group, a mixed ANOVA will be performed for repeated measures with *Time* as within factor (pre-test/post-test/follow-up) and *Group* as between factor (the CBT + VR group/the CBT group).

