Moreover, we will pay attention to the issue of an attrition rate. We are expecting to find a retention rate of at least 80% (78, 79) to avoid that participant loss will bias research outcomes. After that, we will check for any significant difference between the two treatment groups (CBT and CBT + VR) to verify if there is a differential attrition rate. In particular, we will compare the average number of meetings attended by the participants between the two treatment groups through *t*-tests, and we will compare the presence of drop-outs across the two groups through Chi-square tests. Moreover, we will determine if there are any significant differences (at the baseline) between participants who will complete the post-test session and those who will not in order to verify if specific subgroups of participants have a higher drop-out risk. This analysis will be conducted separately for each group. If any significant differences between participants of the two treatment groups will be found, we will verify that systematic attrition does not occur and we will conduct the analyses to verify the effects of the two interventions (CBT and CBT + VR) with the participants who completed the baseline and post-test assessments. Those lost to post tests will be excluded. If significant differences between participants of the two treatment groups will be found for the average number of meetings attended and the treatment drop-out, and participants who will complete the post-test session will be significantly different from those who will not, subsequent analyses will be conducted by using the last observation carried forward (LOCF) to assess the effects of attrition. Furthermore, we will examine within-group changes in outcomes as a function of session attendance to assess the effects of intervention non-compliance on outcomes. These subsequent analyses will be conducted, not excluding participants who will be lost to post-test and by imputing values for the follow-up variables for the participants who will not complete the post-test assessment.

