Despite these strengths, some limitations must be underlined. As a limitation of the study protocol, the use of self-report measures may be affected by the lack of insight/awareness, inability to identify or articulate beliefs/thoughts, and intentional dissimulation in pathological gamblers. However, the use of self-report measures is inevitable, so we chose tests that present good psychometrics properties, and we will consider the MCMI-III validity scales to control the social desirability index and the assessment protocol validity. In order to better control these biases, future studies could consider the introduction of behavioral tasks that in the Alter Game study protocol are not included except in the therapeutic intervention section. Also, the absence of a control group (non-treatment), which could serve to better analyze the efficacy of the integrated intervention, could be a further point to be addressed in the future. A public clinical service cannot omit to offer clinical treatment to a patient with GD for ethical reasons. Moreover, there may be potential threats to the internal validity of the research design due to its longitudinality, with a possible consequent loss of patients. In line with this, we chose a 1-month follow-up to keep the patients as engaged with the study as possible, since the dropout rate in pathological gamblers is high (18, 19). We are aware, however, that this time may not permit the detection of spontaneous recovery. Furthermore, studies could implement a strategy to better control susceptibility to conditioning. Another important consideration deals with the changes due to the COVID-19 pandemic. Indeed, GD is changing: a lot of patients are addicted to online gambling, so some patients that request our treatment may not respond to our inclusion criteria, in particular regarding the type of gambling activities considered in the *Alter Game* study before the beginning of the pandemic. In the future, the development and creation of new virtual environments on online gambling may be needed. The COVID-19 pandemic also brings additional complications: wearing the surgical mask can cause fogging problems to the HMD that compromise the correct use and the ideal fruition of the immersive virtual experience. In addition, the presence of restrictions for the containment of COVID-19 (lockdown, isolation, quarantines) may hamper the possibility of maintaining the 1 session per week that would be required by the study protocol. Another limitation regards the generalizability of the integrated protocol due to the possible presence of cybersickness and specific medical problems. Indeed, patients that present cybersickness during the virtual treatment or clinical problems like epilepsy, visual or hearing impairments, vestibular or cardiovascular or neurological diseases, and schizophrenia or psychotic traits will not be granted access to CBT + VR psychotherapy. Finally, future developments could improve our virtual environments through the insertion of avatars that interact with gamblers, thanks to artificial intelligence. This will be more expensive, but it may be useful to work on the impact of social interaction in the maintenance of GD and to manage situations in which gamblers are invited to eat snacks and drink alcoholic beverages. Indeed, it is known that social isolation and a sense of loneliness are related to problematic gambling (85, 86). Therefore, inserting social interaction in virtual gambling-related environments could be an important development to treat these daily experiences that may be relapse risk factors. Subjects that are socially excluded tend to self-medicate their unpleasant emotional states [e.g., anger, sadness, and anxiety; (87)] through emotion regulation processes (88) that can incorporate gambling too (89). Moreover, some studies highlighted that there is an association between gambling and alcohol use: those who drink alcohol more frequently are more inclined to gamble and to experience negative consequences due to their gambling behavior (90–93), as well as increased speed and duration of the game session (94, 95), increased risky wagering (94, 96, 97), and more rapid depletion of available funds (94–96).

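### Repeated cybersickness ends study participation in the CBT + VR arm only, after randomisation, so the between-arm comparison may be biased and the planned attrition checks do not restore it

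*Protocol article*

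**What the plan says.** All places are in the protocol article.

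- **Randomisation (Intervention):** "Patients meeting the inclusion criteria will be randomly assigned to the CBT group or to the CBT + VR group". This happens before any treatment session.
- **Which arm has virtual sessions (Table 1):** the second therapy cycle is "8 sessions of traditional psychotherapy for CBT group and 8 sessions of psychotherapy based on virtual reality for CBT + VR group". The first cycle is eight sessions of traditional therapy in both arms.
- **Exit rule (Recruitment):** "Patients with the onset of cybersickness for two consecutive virtual sessions will exit from the study". These patients "will be able to undertake a path of psychotherapy as usual in the Addiction Medicine Unit". No study measurement after the exit is mentioned.
- **Efficacy test (Data Analysis):** "a mixed ANOVA will be performed for repeated measures with *Time* as within factor (pre-test/post-test/follow-up) and *Group* as between factor".
- **Analysis set (Data Analysis, attrition paragraph):** the effects of the two interventions are assessed in patients with baseline and post-test data. "Those lost to post tests will be excluded".
- **Fallback (same paragraph):** if the arms differ significantly in meetings attended and in drop-out, and completers also differ significantly from non-completers, then "subsequent analyses will be conducted by using the last observation carried forward (LOCF) to assess the effects of attrition".
- **Discussion (limitations):** "patients that present cybersickness during the virtual treatment or clinical problems like epilepsy" are listed together as patients who will not get CBT + VR. The heading for this is the generalisability of the protocol.

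**The concern.** Stopping virtual sessions and leaving the trial are different events, and the exit rule joins them. The trigger is a reaction to the assigned treatment and cannot arise in the CBT arm. Together with a completer analysis, the rule removes from one arm, after randomisation, the patients who tolerated its treatment worst.

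The question is whether offering CBT + VR does better than offering CBT, and intolerance is part of the effect of that offer. The Discussion puts cybersickness in one sentence with epilepsy and other conditions present at entry. Those conditions act before randomisation and on both arms alike, so they limit only who the result applies to. Cybersickness acts after randomisation on one arm, so it also bears on internal validity. Post-tests that were never collected cannot be recovered at analysis.

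**Working it through.** **1. The plan's own sample size.** Inputs from Recruitment: power 0.95, effect size 0.40 (read as Cohen's f), α = 0.05, n = 58, about 60 recruited. The correlation between measurements is not given; 0.5 is assumed. For the between-group test in a repeated-measures ANOVA with m = 3 measurements:

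λ = f² × N × m / (1 + (m − 1)ρ) = 0.16 × 58 × 3 / (1 + 2 × 0.5) = 13.92, with 1 and 56 degrees of freedom.

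Power is 0.956, and N = 58 is the smallest even total that reaches 0.95. The stated figure is reproduced, so this point does not rest on a sample size error.

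**2. Shift from dropping the exits.** Let p be the share of the VR arm that exits, and g the amount by which their outcome under assignment to CBT + VR would be worse than that of the others, in SD. The mean of those who remain exceeds the mean of the whole randomised arm by p × g. The documents give neither p nor g, and 30 per arm is also assumed. The error rate is the two-sided normal approximation when there is no true difference between arms, with standard error √(1/30 + 1/n_VR) in SD units.

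| Exit share p | Exits of 30 | n_VR | Shift, g = 0.3 | Shift, g = 0.8 | Two-sided error at nominal 0.05 |
|---|---|---|---|---|---|
| 5% | about 2 | 28 | 0.015 SD | 0.04 SD | 0.050–0.053 |
| 10% | 3 | 27 | 0.03 SD | 0.08 SD | 0.051–0.060 |
| 20% | 6 | 24 | 0.06 SD | 0.16 SD | 0.056–0.090 |

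Example for the last cell: 0.20 × 0.8 = 0.16; √(1/30 + 1/24) = 0.274; 0.16 / 0.274 = 0.58; two-sided error 0.090. If g = 0, the shift is zero at every p.

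**3. Would the LOCF fallback be reached?** It needs several significant results together, so its probability cannot exceed the power of the chi-square test on drop-out alone. Exact enumeration at 30 per arm, without continuity correction:

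| Drop-out CBT v CBT + VR | Power |
|---|---|
| 10% v 20% | 19% |
| 20% v 30% | 14% |
| 10% v 30% | 50% |
| 20% v 40% | 39% |

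**4. Would LOCF repair the comparison if reached?** Table 1 schedules the questionnaires at pre-test, post-test and follow-up only. For a patient who exits during the virtual cycle, the last value of GRCS or MGSES is therefore the pre-test, and LOCF assigns zero change. That patient has by then had eight CBT sessions and at least two virtual sessions. If such patients in fact gained h SD, LOCF understates the VR arm by p × h. LOCF is right only when h = 0.

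**5. Precision.** The margin is 60 − 58 = 2 patients. Three exits (10% of 30) leave 57. Under the step 1 reconstruction, with arms of 30 and 27, power is 0.952; with six exits (30 and 24) it is 0.940. The stated n is missed, but the loss of power is small.

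**The case against.** The strongest case against the point has five parts.

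- **Attrition is recognised.** The Data Analysis section plans a drop-out comparison by arm, a comparison of meetings attended, completer checks and an analysis that keeps those lost. This stands: it would be wrong to say the plan ignores differential attrition. What remains is that the safeguard is conditional, seldom reached at this size, and does not recover the missing scores.
- **The direction is not proven.** A reader might infer that the rule necessarily favours CBT + VR. The documents do not support that, because nothing in them links cybersickness to outcome.
- **Zero gain for exits is an extreme case.** A reader might take exits to gain nothing while the rest gain a full 0.8 SD. That sits badly with eight CBT sessions already received and usual psychotherapy available afterwards. It is the upper end of the range, not the expected case.
- **The CBT arm is not unselected.** The completer rule applies to both arms, and the Discussion expects high drop-out among gamblers. The net bias is the difference between two selections; the table shows only the part that the exit rule adds. The expected retention of at least 80% would by itself allow 0.8 × 60 = 48 patients, so falling below 58 is not peculiar to cybersickness.
- **Exits may be few.** The environments were designed to limit cybersickness, immersion is about 20 minutes, patients with vestibular or neurological problems are screened out, and two consecutive affected sessions are needed. This argues against the 20% end but fixes no rate.

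That exits have no post-test is also an inference, since the article does not say so outright. It is the natural reading of leaving the study, and nothing in the text says otherwise.

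**Conclusion.** The concern holds in a limited form. As written, the plan makes a treatment-caused, one-sided exit after randomisation and then analyses completers, so the arm comparison may be biased. It favours CBT + VR only if poor tolerators would have done worse; otherwise the cost is precision, and that cost is small. Under assumed exits of 5–20% of about 30 patients and an outcome 0.3–0.8 SD worse, the shift is about 0.015–0.16 SD. At 5–10% exits the effect on the error rate is slight (at most about 0.060); only the upper corner of the range is notable (about 0.090). All of this rests on assumed rates, an assumed 30 per arm and selection through this rule alone.

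The reason to act is less the expected size than that the trial, as written, would stop measuring the very patients who could show whether a bias exists. Listing cybersickness only under generalisability understates the issue.

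**What to change.** Leave the rule on ending virtual sessions as it is; nothing here questions it. Change the following:

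1. In Recruitment, replace the exit from the study with a statement that these patients stop virtual sessions but remain in the trial, with usual psychotherapy as already foreseen.
2. State that they complete the post-test (week 19) and the 1-month follow-up questionnaires.
3. In Data Analysis, state that they are analysed in the CBT + VR arm as randomised in the primary comparison, without a prior significance test on attrition.
4. Report the number of cybersickness discontinuations.
5. In the Discussion, name the issue as a threat to the arm comparison as well as to generalisability.

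The cost is a wording change and two questionnaire visits for a few patients who can remain in the same unit's care. The sample size is unchanged. The change must be in place before such exits occur.

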### Interventional Methods

#### Intervention

Patients will be recruited when they access the Addiction Medicine specialist service “Colma il Gap” for GD at the G. B. Rossi Hospital in Verona, Italy. The selection of the sample will be based on the inclusion criteria. The selection of the patients who may be involved in the study will attend the following procedures. At the first access to the service, the patient will sign the informed consent and will be interviewed for the collection of anamnestic, life/family history, and clinical and gambling history details. We will assess legal and illegal substance use and the presence of addiction during the first psychological examination through a structured interview. It is important to capture sub-clinical factors related to the use of substances that could influence response to VR as well as situations linked with relapse. At the second visit, the questionnaires will be administered to the patient, in a self-completion mode, in the following order: MCMI-III, BIS-11, SOGS, GRCS, and MGSES. If the expected inclusion criteria will not be met, the patient will be excluded from the study but will be taken care of according to the usual treatment.

Patients meeting the inclusion criteria will be randomly assigned to the CBT group or to the CBT + VR group. The CBT group will follow a full cycle of psychotherapy that will consist of 16 weekly sessions, lasting 60 min and will make use of techniques belonging to an evidence-based cognitive-behavioral approach. For the CBT + VR group, there will be a first cycle of traditional psychotherapy that will consist of 8 weekly sessions, each lasting 60 min, which will also make use of evidence-based cognitive-behavioral approach techniques. Following this, psychotherapy based on virtual exposure will be carried out, which will again comprise 8 weekly sessions, marked by: systematic desensitization therapy in virtual reality exposure therapy, cognitive restructuring, and emotional management/literacy. Each virtual session will last 60 min, 20 min of which will be dedicated to virtual exposure. About 20 mins is the recommended limit of the duration of immersions in virtual reality because eyestrain and headache may occur for longer exposures (76, 77). We adopted this safety limit at least until empirical data document the safety of VR immersion with gamblers (10). An extinction process needs more time to originate, but limiting the duration of the immersion is necessary due to ethical considerations (10).

The virtual session will be structured as follows. In the first session, the virtual protocol will be presented to the patient, and virtual training will be carried out to provide the skills related to the use of the instrumentation (Figure 11). Biofeedback parameters will also be measured 5 min before the session. From the second to the eighth sessions, the biofeedback parameters will be measured 5 min before the beginning of the session (in the study, the baseline rate), and the measurements will be resumed during the entire exposure to the virtual environment. The patient will be asked about the intensity of the craving felt during both measurements and at the end of each session *via* VAS. As mentioned above, the technique used in conjunction with virtual cue exposure therapy will be systematic desensitization, which is a psychotherapeutic CBT treatment consisting in alternating phases of exposure to the trigger cues to phases of bodily relaxation, with the aim of reinforcing the relaxation response even in the presence of specific reactive cues (78, 79).

